## Methods

The primary aim is to determine the incidence of paediatric patients presenting with critical events associated with tracheal intubation. Table 1 presents definitions of critical events used in this study. As an observational study, CRICKET remains inherently susceptible to confounding by indication, although its large sample size and detailed, standardised data collection will help to characterise and mitigate this potential bias. Analysis of these events will focus on identifying clusters of events and risk factors for frequently occurring events. For example, in some conditions, critical events might be characterised by two or more airway-related complications occurring in close temporal proximity during the same intubation episode, suggesting a connected cascade (such as desaturation followed by bradycardia and hypotension) rather than isolated, unrelated events. Similarly, clusters of particular events might be identified in a specific subgroup of patients. This may allow us to identify independent risk factors and, consequently, children at particular risk for critical events.

**Table 1 tbl1:** Definition of critical events associated with tracheal intubation. CPAP, continuous positive airway pressure.

Definition of tracheal intubation-associated critical events	
‘Critical events’ in this study and time frame	Any episode of occurrence during tracheal intubation requiring a medical intervention from the start of anaesthesia until the end of anaesthesia (defined as handover to either the PACU, the paediatric or neonatal intensive care unit, the ward, or discharge home straight from anaesthesia care).
Severe hypoxemia	SpO_2_ <85% or >20 points below initial value for at least 60 s.
Severe bradycardia	Persistent bradycardia for at least 1 min: • 0–3 months old: HR <80 beats min^−1^ • 4 months–2 yr: HR <60 beats min^−1^ • 2–10 yr old: HR <40 beats min^−1^ • 10–16 yr old: HR <30 beats min^−1^
Oesophageal intubation	Tracheal tube placed in the oesophagus diagnosed by (video-) laryngoscopy, absence of sustained EtCO_2_ trace, absence of lung ventilation (auscultation or absence of chest excursions) causing a decrease in oxygenation.

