Laryngospasm	Complete airway obstruction associated with rigidity of the abdominal and chest walls and leading to unsuccessful child’s ventilation, or glottic closure associated with chest movement but silent unsuccessful child’s respiratory efforts and assisted ventilation, unrelieved in both situations with simple jaw thrust and CPAP manoeuvres and requiring the administration of medication (propofol, suxamethonium etc.), tracheal (re)-intubation, or both.
Bronchospasm	Increased respiratory effort, especially during expiration, and wheeze on auscultation. Episode of bronchospasm requires the administration of a bronchodilator.
Stridor after extubation	Severe inspiratory flow limitation with sternal retraction, intrathoracic pressure swing, and potentially cyanosis occurring after extubation with or without the administration of oxygen; i.v. steroids, epinephrine (nebulisation), or both; or tracheal intubation. This can be documented clinically or with diagnostic examination, with persistence of symptoms.
Obstruction of tracheal tube	Obstruction of tracheal tube needing lavage or tube exchange.
Airway bleeding	Acute bleeding from nose, arytenoids, or pharynx causing obstruction or risk for pulmonary aspiration.
Can’t intubate can’t oxygenate (CICO)	Situation when there is failed intubation and failure to adequately oxygenate using facemask ventilation or supraglottic airway device resulting in increasing hypoxemia in an anaesthetised and paralyses patient.
Severe bradycardia/cardiac arrest	Cessation of circulation (no pulse) or severe bradycardia requiring chest compressions, during the intubation/extubation manoeuvres.
Pulmonary aspiration	Presence of non-respiratory secretions (gastric, particulate, blood) in the airway as evidenced by (video-)laryngoscopy, suctioning, or bronchoscopy or radiologic signs.
Pneumothorax/pneumomediastinum	Air in the thorax, mediastinum, or both as a consequence of tracheal intubation and ventilation, causing lung collapse or mediastinum dislodgment diagnosed by lung ultrasound, X-ray, or both.
Negative pulmonary oedema	Non-cardiogenic pulmonary oedema that results from the generation of high negative intrathoracic pressure needed to overcome upper airway obstruction.

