### Causal model for identifying determinants of critical events

Recent cross-sectional studies have suggested a relationship between the risk of critical events in paediatric tracheal intubation and patient anthropometric characteristics, anatomical variations in the airway, the presence of comorbidities, and the skill and experience of the healthcare provider. Despite these findings, no study has investigated the causal relationship between these events and the factors underlying their occurrence. Identifying and understanding the determinants of critical events during paediatric tracheal intubation are crucial for recognising and managing them effectively, thereby enhancing the quality and safety of tracheal intubation and improving the outcomes of young patients.

To estimate causal effects, we must appropriately identify, select, and include all relevant confounding variables.^10^ We will construct a directed acyclic graph (DAG) to visually represent the causal structure of our research question.^11^ A DAG provides a non-parametric depiction of cause–effect relationships and enables us to identify variables that may plausibly confound the association between exposure and outcome.^12^^,^^13^ This approach offers an intuitive visual framework grounded in rigorous causal inference methodology.^14^^,^^15^ In the CRICKET observational study, we will develop a causal model to identify factors associated with critical events during paediatric tracheal intubation. We will use a DAG to identify potential confounders that influence the relationship between critical events and their determinants. We will draw on expert opinion to define known causal pathways and exposures. We will also perform sensitivity analyses to evaluate the influence of unmeasured confounding on our findings. We will construct the DAG using the R package [CRAN (open source), Radboud University & Medical BioSciences, Nijmegen, The Netherlands (Textor)] *dagitty*,^15^ based on the web-based DAGitty platform. To minimise bias in interpreting the results, we will develop the causal model and identify the exposures of interest in parallel with the principal statistical analysis, once recruitment is complete and data cleaning has been finalised.

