### Statistical analysis

A descriptive analysis of the data will be carried out, using counts and percentages to summarise categorical data and median (interquartile range) to summarise continuous data.

The incidence of critical events will be estimated and reported together with a 95% confidence interval. Furthermore, critical event incidence will be provided for different age categories, operator’s experience, operator’s speciality, and centre volume.

In terms of risk factor analysis, a univariable and multivariable mixed-effect logistic regression model will be computed based on possible predictors, which include for example age (≤12 months), weight (≤10 kg), number of attempts (more than two), presence of comorbidities (ASA score ≥3), comorbidity related to airway management (e.g. relevant syndromes), expected difficult intubation, type of anaesthesia induction (i.v. or inhalation), no neuromuscular blocking agent given, airway surgery or ears, nose, throat (ENT) surgery, and experience level of the person performing tracheal intubation. Appendix 1 lists the relevant factors used for primary and secondary analyses. Goodness-of-fit, calibration, discriminatory capacity, and predictive skill of the regression models will be assessed using Nagelkerke pseudo-*R*^2^, calibration belts, area under the receiver operating characteristic curve (AUROC), and Brier Score, respectively.

The target sample size for CRICKET is informed by statistical considerations and the practical constraints of conducting a large, multinational observational study. Although the sample size calculation indicates that approximately 105 000 cases are required to estimate an event rate of 0.5–1% with acceptable precision, the achievable enrolment also depends on centre capacity, case volume, and the coordinated activation of participating sites across multiple jurisdictions. Recruitment will therefore proceed sequentially from January 2024 to December 2025, with each centre contributing a consecutive 3-month sampling window once local approvals and resources are in place. If the required sample size is not reached by the end of 2025, the steering committee may extend the recruitment period or, alternatively, close enrolment and proceed with analysis of the accrued data, depending on the number of events captured and the resources remaining.

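### The multivariable risk-factor model names number of attempts as a predictor, although attempts can mediate the event or result from it; keep them out of the main model

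*Protocol article*

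**What the plan says.** The Statistical analysis section of the protocol article states that "a univariable and multivariable mixed-effect logistic regression model will be computed based on possible predictors, which include for example age". The examples that follow include "number of attempts (more than two), presence of comorbidities (ASA score ≥3), comorbidity related to airway management", then expected difficult intubation, type of induction, "no neuromuscular blocking agent given, airway surgery or ears, nose, throat (ENT) surgery", and "experience level of the person performing tracheal intubation". For the full set of factors it refers to Appendix 1, which is not shown. Model performance is to be judged by Nagelkerke pseudo-R², calibration belts, AUROC and Brier score.

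In Methods, the stated hope is to find independent risk factors and, through them, the children at particular risk. Table 1 there lets an event fall anywhere from the start to the end of anaesthesia. Its definition of oesophageal intubation begins "Tracheal tube placed in the oesophagus diagnosed by (video-) laryngoscopy". CICO requires a failed intubation "resulting in increasing hypoxemia in an anaesthetised and paralyses patient". Laryngospasm can qualify through the need to intubate the trachea, including a repeat intubation.

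A separate section, Causal model for identifying determinants of critical events, says "To estimate causal effects, we must appropriately identify, select, and include all relevant confounding variables" and plans a directed acyclic graph (DAG). The graph is to be built alongside the main analysis, after data cleaning. The article does not say that it governs the predictor list in the Statistical analysis section.

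**The concern.** The listed predictors are of two kinds. Age, weight, ASA class, expected difficulty and the operator's experience are settled before the first laryngoscopy. The number of attempts is produced during the procedure and depends on those same factors.

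Putting both kinds into one multivariable model raises three problems:

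- **Mediation.** If inexperience raises risk partly by causing more attempts, adjustment for attempts removes that part from the odds ratio for experience.
- **Reverse causation.** If an event forces a further attempt, the attempts odds ratio partly measures the effect of the event on attempts. Conditioning on such a variable also distorts the other coefficients.
- **Discrimination.** A variable that records part of the outcome raises the AUROC, yet it is not available when a child at risk has to be identified.

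At stake are the adjusted odds ratios for factors that readers may act on, above all operator experience. A large sample does not help: the bias stays and the interval around it narrows.

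**Working it through.** The plan gives no figure on this point, so there is nothing to reproduce. The text settles whether the problem exists. The arithmetic shows only its possible size, and every numerical input below is assumed.

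**1. Order of attempts and event.** The event window covers the whole anaesthetic. Under Table 1, oesophageal intubation is itself a misplaced tube, CICO contains a failed intubation, and laryngospasm may end in re-intubation. For these events attempts can be part of the event or come after it. For others, such as stridor after extubation, attempts come first. The article does not restrict the predictor to attempts made before the event.

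**2. Mediation alone.** Assume more than two attempts in 1% of cases with experienced and 4% with inexperienced operators, an odds ratio of 8 for attempts, a direct odds ratio of 1.2 for inexperience, and a risk of 1% in the reference cell (odds 0.010101).

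- Experienced, more than two attempts: odds 0.010101 × 8 = 0.080808, risk 0.074766.
- Inexperienced, two or fewer: odds 0.010101 × 1.2 = 0.012121, risk 0.011976.
- Inexperienced, more than two: odds 0.080808 × 1.2 = 0.096970, risk 0.088398.
- Overall risk, experienced: 0.99 × 0.01 + 0.01 × 0.074766 = 0.010648.
- Overall risk, inexperienced: 0.96 × 0.011976 + 0.04 × 0.088398 = 0.015033.
- Odds ratio without attempts in the model: (0.015033/0.984967) / (0.010648/0.989352) = 1.42.
- Odds ratio with attempts in the model: 1.20.

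A simulation of 2 million cases with these inputs gave 1.43 and 1.21.

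Now let the whole effect run through attempts: 2% against 8%, odds ratio 10, reference risk 0.8%, direct odds ratio 1. The risk with more than two attempts is 0.074627. The overall risks are 0.98 × 0.008 + 0.02 × 0.074627 = 0.009333 and 0.92 × 0.008 + 0.08 × 0.074627 = 0.013330. The odds ratio is 1.43 without attempts and 1.00 with them.

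**3. Reverse causation alone.** Suppose attempts have no effect on risk, but more than two attempts are seen in 10% to 20% of cases with an event against 2% without.

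- Odds ratio: (0.10/0.90)/(0.02/0.98) = 5.4, and (0.20/0.80)/(0.02/0.98) = 12.2.
- AUROC of this variable by itself, (1 + sensitivity − false-positive rate)/2: (1 + 0.10 − 0.02)/2 = 0.54, and (1 + 0.20 − 0.02)/2 = 0.59. A variable with no relation to the event scores 0.50.

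**4. Sensitivity to harsher inputs.** If 30% of events lead to more than two attempts over a background of 1%, the frequency among events is 1 − 0.99 × 0.70 = 0.307. The spurious odds ratio is then (0.307/0.693)/(0.01/0.99) = 44. Adding this 30% to the first setup in step 2 moved the simulated odds ratio for inexperience from 1.46 without attempts to 0.87 with them.

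**5. Relaxant and CICO.** A child given no relaxant cannot meet the CICO definition. Suppose the true odds ratio for no relaxant is 1, the composite risk in paralysed children is 1%, and a share f of their events are CICO and meet no other definition. The risk without relaxant is then 0.01 × (1 − f), and the composite odds ratio is [0.01(1 − f)/(1 − 0.01(1 − f))]/(0.01/0.99). This gives 0.99, 0.95 and 0.90 for f = 1%, 5% and 10%.

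**The case against.** The strongest defence has five parts.

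- **The list is illustrative.** It is given by way of example, and Appendix 1, which may stage or trim it, is not shown. So a reader may not infer that the final model is one fixed, mutually adjusted list. Attempts are nevertheless expressly named for the multivariable model, so this is a stated choice and not an omission.
- **The model is associational, and causal work is assigned to the DAG.** That is a fair reading, and a DAG is the right tool for telling mediators from confounders. But the article does not link it to this predictor list. A purely predictive reading does not rescue attempts either, since the count is unknown before intubation.
- **Unadjusted results are also planned.** Univariable models and incidence by operator experience will show the unconditional association. This stands and limits the harm.
- **Attempts are a legitimate exposure.** The introduction notes that guidelines advise limiting them, and for late events they do come first. This stands too, and it supports a separate analysis of attempts.
- **The sizes are assumed.** This also stands. A reader might infer from step 4 that the sign for experience will reverse, or that attempts are usually the result of the event. The documents support only that attempts can be its result, and give no frequency.

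On CICO, a reader might infer a regression of CICO on relaxant use with an odds ratio of zero by construction. No such model is planned: Methods directs the risk-factor work at events that occur often. In the composite, an unparalysed child who cannot be intubated or oxygenated can still count under severe hypoxemia, so the shift should be smaller than step 5 shows.

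**Conclusion.** The concern holds for the multivariable risk-factor model. As written, it may adjust upstream factors for a variable that can mediate their effect and can be produced by the event. Its adjusted odds ratios would then not answer the question about independent risk factors, and its AUROC would look better than a usable model's. The direction of the mediation effect follows from the structure, provided that inexperience leads to more attempts and attempts raise risk. Its size does not: about 1.4 to 1.2 for inexperience, and a spurious 5 to 12 for attempts, are illustrations on assumed inputs.

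The primary incidence and its interval, the incidence by operator experience and the univariable estimates for the upstream factors do not depend on this choice. A reader might infer that the study's main result is at risk; it is not. This is a recommended change to a secondary analysis. The CICO point is minor and calls for no more than a sensitivity analysis.

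**What to change.** - Fit the main multivariable model only on factors fixed before the first laryngoscopy. State that the planned DAG chooses the adjustment set for each exposure of interest.
- Report the number of attempts descriptively, or in a separate model limited to attempts made before the first event, where the case report form recorded the timing.
- Present AUROC, calibration and Brier score for the model without attempts.
- Repeat the relaxant estimate with CICO left out of the composite, as a sensitivity analysis. Leave the Table 1 definition unchanged, because data have already been collected under it.

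The cost is revised analysis wording, one extra model, one sensitivity run and a less favourable AUROC. No new data are needed, and the change can be made before the database is locked for analysis.

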### Data management

Patient characteristics will be obtained from the anaesthesia record. All study data will be directly recorded in the CRF on paper or electronically, which are considered as source data. Dedicated study personnel will check all data entry into the CRFs for their validity and completeness on a weekly basis. External monitoring will not occur, as this is an investigator-initiated multicentre study and quality measures must be implemented at each study centre.

Study data generated in participating centres will be collected and managed using a web application on the servers of the University of Padova using the study management software REDCap®, set up on a dedicated website with all the guarantees of security requirements. Study data will be collected and managed using REDCap® electronic data capture tools, developed, tested, validated, and hosted at the Department of Cardiac-Thoracic-Vascular Sciences and Public Health, University of Padova, Italy. REDCap® is a secure, web-based software platform designed to support data capture for research studies, providing (1) an intuitive interface for validated data capture; (2) audit trails for tracking data manipulation and export procedures; (3) automated export procedures for seamless data downloads to common statistical packages; and (4) procedures for data integration and interoperability with external sources. Access to REDCap® will be granted only to data collecting staff of participating centres, in accordance with the procedures outlined in the protocol. Each participating centre is granted access only to the patient data it has generated and recorded on the REDCap® platform. The data will be recorded using an encrypted data connection (HTTPS) in input masks via a web browser or mobile app.

Study data will be archived for a minimum of 10 yr after study termination or premature termination of the clinical trial.

### Ethics

The CRICKET study has been approved by Swiss Ethics Committee (approval no. 2023-00246 on 9 March 2023). Any amendment to the protocol must be approved by the relevant ethics committees/authorities. The study was prospectively registered at www.clinicaltrials.org (identifier: NCT 05804188).

Study centres will enter data in the centralised database and will have access only to their own institutional data. The centralised database will be established in Padua, Italy, and will be subject to the data protection laws in force in Europe (General Data Protection Regulation, 2016/679). Access to the data will only be granted for data control and statistical analysis by the person responsible for the centralised database. By these measures, we intend to achieve maximal protection of patient and institutional data.

### Publication and dissemination policy

The results will be published in a peer-reviewed scientific journal to provide new knowledge that may support the development of targeted quality improvement strategy in paediatric airway management, including modifications to clinical strategies, enhanced training, or addressing technical gaps. Final decision on publishing the results will be kept by the steering committee of the study. Authors of the publication will be team members of the consortium who contributed to the design, conduct, or analysis of the study and who approved the final version of the manuscript. International, national, and local investigators will be listed as collaborators (‘CRICKET Investigator Group’) in all publications that include CRICKET data, including secondary and ancillary analyses for subsequent publications.

## Patient and public involvement

Patients and the public were not involved in the design, conduct, or reporting, or dissemination plans of this research.

